**Background:**

The Washington, DC Department of Corrections (DOC) Central Detention Facility (CDF) has conducted routine opt-out HIV testing since 2006. Approximately 3% of those screened for HIV were infected^1^, of which one-third were newly diagnosed infections^2^. These data strongly supports the application of Seek, Test, and Treat within jails in order to help support linkage to care among detainees with known HIV infection upon release back into the community.

For HIV-infected inmates, release into the community has been shown to be detrimental to antiretroviral therapy (ART) adherence and maintenance of HIV care^3-5^. The benefit of treating HIV-infected jail detainees is diminished if treatment cannot be continued and maintained after community re-entry. New and innovative methods including tools for real-time communication need to be developed to ensure ART adherence and linkage to care for HIV-infected jail detainees being released. To address these needs, we propose to develop information and communication technology (ICT)-based tools to facilitate the delivery of education and counseling regarding the importance of ART and HIV care adherence. If these tools are found to improve adherence to ART, enhance linkage to community care, and are found to be cost effective, they have the advantage of being readily disseminated to a broad array of correctional facilities.

**Specific aim:**

This study will investigate whether an intervention (CARE+ Corrections) delivered to HIV-infected detainees within the DC Department of Corrections (both the Central Detention Facility and the Central Treatment Facility (CTF)) and recently-released ex-detainees in the community can improve linkage to community HIV care and adherence to HIV medications after release. The intervention is modeled after **CARE**, which is a technology based HIV-counseling tool used in other settings. We have adapted CARE to create **CARE+ Corrections**, a tool designed specifically for incarcerated and recently-released populations. Counseling via CARE+ Corrections will be delivered pre-release or within 6 months after release and will consist of a one-time computerized counseling session delivered by a tablet computer that will provide interactive counseling related to risk behaviors, linkage to community HIV care, and HIV medication adherence. This counseling session will be approximately 30-40 minutes in length and will be conducted within the DOC facilities or in a community setting. CARE+ Corrections will be coupled with a cell phone/text messaging intervention that will be delivered in the community, after release from a correctional facility. The cell phone/text messaging intervention will consist of participants receiving a cell phone, or use of an existing personal cell phone, that the study team will use to deliver reminders about HIV medical appointments and taking HIV medications. The study is a randomized controlled trial where one-half of the participants will receive the intervention (CARE+ Corrections plus the community-based cell phone/text messaging intervention) either inside the correctional facility, in addition to standard discharge planning services, or in the community right after release. The other one-half of study participants will view an educational video related to the prevention of overdose following release from the correctional facility, in addition to standard discharge planning services, or in the community right after release. We will follow all participants for 6 months after release/study entry during which we will conduct follow-up assessments at 12 week and 24 week appointments to determine if the linkage to care and adherence to HIV medications were higher in the intervention arm.

**Enrollment goal:**

We plan to enroll, over a 2-year study period, up to 150 HIV-infected detainees and recently-released ex-detainees within the DC Department of Corrections facilities and in the community. Participants will be enrolled inside the DC Department of Corrections (DOC) facilities and or in other private designated space (e.g., within a local CBO or in GWU research clinic space) in the community within 6 months of release from a correctional facility.

Detainees will be recruited from the Central Detention Facility (CDF) or from the Correctional Treatment Facility (CTF), both under the jurisdiction of the DC DOC. These facilities together will be referred to from here on as “DOC”. Correctional facilities refer to jail, prison, halfway houses and other restricted settings. Recently-released ex-detainees will be recruited from local community-based organizations (CBOs) that work closely with returning citizens and venues that cater to this population (see below) (see attached letter of support from the Visitors’ Services Center: Appendix O).

**Study approval:**

Prior to study implementation, the study protocol will be approved by the George Washington University IRB (primary), the Miriam Hospital IRB, and the Office of Human Subjects Research Protection (OHRP). Following these approvals, the protocol will be reviewed and approved by the Washington, DC DOC.

**Study procedures:**

- See Appendix A for a diagram of study flow.
- Recruitment: The study will be conducted in a private space designated by the DOC Administration and Security staff or designees for detainees in DOC facilities, or in a private space (e.g., within a local CBO or in GWU research clinic space) for community-recruited individuals.

Potential participants will be HIV-infected detainees and ex-detainees. Our study will include the following recruitment methods. Potential participants will be recruited in the DC DOC facilities or through partnering CBOs or community referrals. Community participants will also be recruited from a variety of health and non-health related organizations and venues that cater to this population, including offices working with returning citizens, local establishments geared toward meeting the needs of this group, local newspaper advertisements, electronic advertisements including Craigslist.com, fliers posted at frequently-visited venues, etc, as well as through street-based recruitment. We will also contact interested individuals registered in the GWU Potential Participant Cohort (IRB #031140) for screening for this study.

- To identify potential participants inside the DC DOC facilities, the following strategy will be used. DC DOC discharge planners and case managers currently maintain a list of inmates who are scheduled to be released to the community and are slated for a medical visit, HIV discharge planning or a meeting with a case manager. The medical staff, discharge planners, case managers, and/or others working with soon-to-be released detainees will present a flier (see Appendix B: Recruitment Fliers) to inmates and refer interested individuals to meet with GWU staff in a pre-designated, private location in the DOC facilities to learn more about the study. The inmate would be screened for eligibility and consented, if willing and eligible to join the study. GWU staff will not have access to the pre-release list or names of individuals prior to the consent process.
- For individuals in the halfway houses and other correctional facilities who might be eligible, fliers may be distributed and posted (see Appendix B: Recruitment Fliers) to residents to refer those interested in the study to contact GWU staff to learn more about it.
- To identify potential participants in the community, the following strategy will be used. The GWU staff will work with partnering CBOs in the Washington DC area who operate in local correctional facilities and have direct contact with inmates, individuals who are in other correctional settings or other returning citizens in the community. (Referrals may also be made through word of mouth.) Representatives from the DOC and other correctional settings and partnering CBOs who work within the jail may offer inmates about to be released from these facilities or recently-released consumers they serve a flier (see Appendix B) about our study. They will refer interested individuals to meet with GWU staff after release in a pre-designated, private space (e.g., at local CBOs or in GW research clinic space) to learn more about the study. The ex-detainee will be screened for eligibility and consented, if willing and eligible to join the study. GWU staff will not have access to the names of individuals prior to the consent process.
  - For participants recruited inside the DC DOC facilities, a “post-release” visit (please see below) will be scheduled based on their release date. For participants enrolled in the community, follow-up visits will be scheduled based on the date of completion of the baseline visit.

***Screening and enrollment visit:***

- An interviewer-administered eligibility screener will be used to determine eligibility of potential study participants (see Appendix E: CAPI Questionnaires—eligibility screener included in baseline CAPI Questionnaires).
- Before administering the eligibility screener, a Verbal Informed Consent will be administered (see Appendix C: Screening Verbal Informed Consent Form). For recruitment conducted inside the DC DOC facilities, once the detainee has provided verbal consent, the GWU study RA will administer the eligibility screener. For recruitment conducted through partnering CBOs or community referrals, GWU staff will ask individuals to confirm their HIV status. For these individuals, GWU staff will also confirm that their release from a correctional facility occurred within the past 6 months. Once HIV positive status and date of release within the past 6 months has been confirmed and the ex-detainee has provided verbal consent, the GWU study RA will administer the eligibility screener.

Eligibility criteria include:

- Currently detained in DC DOC facility or released from the jail, prison, halfway house or other correctional facility 6 months ago or less
- Age ≥ 18
- English speaking
- Able to provide informed consent for research participation
- Anticipated release from jail, prison, halfway house or other correctional facility to the community (or living in the community if recently released ex-detainee)
- Confirmed to be HIV-infected by self-report
- Live in the metropolitan Washington, DC area.
- Able to read at 8^th^ grade level as assessed by brief literacy screen (embedded in Eligibility screener)

Exclusion criteria include:

- Expected release to a restricted setting (or currently living in a restricted setting if recruited in the community) that limits/restricts cell phone use, such as a residential drug treatment program, sober house, half-way house, or similar. If an individual is currently housed in a halfway house or other restricted setting, they may be eligible for recruitment after release from this facility.
- Detainees or recently released ex-detainees who meet the eligibility criteria will be offered the opportunity to participate in the study. Participation will be voluntary. Detainees who do not meet eligibility criteria or choose not to participate will return to their previous location as determined by the security staff. The standard of care for HIV discharge will not be affected by their refusal to participate.
- Detainees or recently released ex-detainees who elect to participate will complete written, informed consent for study participation with the study research assistant (RA). The informed consent form will be read aloud to the participant (see Appendix D: Informed Consent Forms). A copy of the informed consent will be provided to the participant. For participants recruited inside the DC DOC facilities, the GWU RA will provide the option of leaving their copy with the RA in order to protect confidentiality and receiving it at their next study visit after being released to the community. The RA will maintain a file of completed informed consents at the administrative study office at the Department of Epi/Bio at GWU in a locked file cabinet.
- Consenting study participants will also be asked to provide consent for release of medical records from the DC DOC facilities and any community medical providers that they may come into contact with during the course of the study.
- A study locator form requesting contact information for participants after release in the community will be completed. In the case of recently released ex-detainees the locator form will include participants’ current and anticipated contact information.

For community-recruited individuals, the baseline visit will occur within one study visit as much as possible. However, for individuals recruited inside correctional facilities, the baseline visit may be split across multiple time points if necessary, as determined by constraints of that facility.

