    - Statistics on OD upon release
    - Steps to preventing overdose
      - seeking treatment
      - make a plan to stay clean
    - Education about opiate, tolerance and purity, and danger of mixing opiates with other drugs/alcohol
    - Signs of overdose
    - How to respond to an overdose:
      - chest noogies
      - call 911
      - rescue breathing
      - Narcan
      - rescue position

The RA will then review the post-release/follow-up study procedures with the study participant, which includes collection of locator information, description of the post-release visit (see below), and explanation of continued follow-up.

Participants recruited inside the facility will receive typical discharge planning services as determined by the staff at the facility. For example, typical discharge planning for the DOC includes:

- 30 day supply of HIV medications (if patient is prescribed HIV medications)
- Appointment with community provider at Unity Health Care (contracted provider within the DC Jail) or referral to another community HIV provider
- DOC medical records

For participants in the intervention arm, recruited in the community, study staff will provide a cell phone and training on the text messaging portion of the intervention (described below).

At this visit, a post-release/follow-up appointment will be made for all study participants. In addition, study participants will be given study materials that provide information on the study clinic location, 800-number to call and make an appointment. In addition, participants recruited inside the facility will be given a flier reminding them to check in with the study staff upon release (See Appendix G).

Participants recruited in the community will receive a $50 incentive for completion of the baseline visit. Participants recruited in the correctional facility will receive their $50 incentive at the post-release follow-up visit (see below).

- Medical Chart Review: With subjects’ prior consent to the release of their medical records (see Appendix K: Medical Records Release Form) as included in the Informed Consent Form (Appendix D), relevant data will be collected from correctional facility and community provider medical records. Specific measures that will be abstracted include data from the 12 months prior to study enrollment related to HIV clinical care, comorbidities and sexually transmitted infections, and ancillary services (see Appendix I: Medical Records Abstraction Form).

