4. At the end of the study visit the staff will provide a list of referrals, a $50 incentive for completion of the visit, $10 incentives for every successful monthly phone call since the previous study visit, and a voucher for transportation. The incentives will be in the form of American Express Gift Cheques.
5. After the study visit, the study staff will confirm the participant’s engagement in care by contacting his/her medical provider and obtaining data on appointments, plasma viral load, CD4 data if available and antiretroviral medication prescriptions, given approved medical release from the participant.

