The longitudinal nature of the study (containing a baseline assessment before intervention and two follow-up visits after jail release) will result in repeated assessments of primary outcomes (plasma viral load suppression at Visits 2 and 3) and secondary outcomes (e.g., proportion linking to community HIV care at 30 days, 60 days, 90 days, etc.). These outcomes will be analyzed in the unified framework of generalized linear models (GLMs) with appropriate link functions (logit for dichotomized outcomes, e.g. linkage to care, detectable PVL; identify link for continuous outcomes, e.g. log-transformed PVL; or log link for count outcomes, e.g. # of non-main sexual partners). The setup of GLMs involves relating the expected outcome to a linear function of explanatory covariates, where the explanatory covariates will include a dummy variable encoding the treatment (=1) versus control (=0), dummies for study site and gender, relevant demographic covariates, and their interactions. Depending on the analysis objectives, three GLM model structures will potentially be used: 1) *Marginal models* will be used to analyze population-level intervention effect. Within-individual correlation of repeated measures will be accounted for using Generalized Estimating Equations (GEE),^6,7^ which yields consistent parameter estimates and robust standard error estimates. 2) *Random-effect generalized linear models* will be used to estimate the intervention effect at the individual-level.^8^ For those outcomes with only one follow-up visit, the model will be estimated using conditional logistic regression for binary outcomes or difference-on-difference regression for continuous outcomes for better estimation efficiencies. 3) *Markov transition models* will be used to investigate the intervention effect on the individual behavior change as previously conducted by this group,^9^ and includes the prior history of the outcomes as regression covariates; therefore, the transition model emphasizes more the effect of the intervention on outcome changes given the prior value of the outcome. Using these model setups, we will examine the different aspects of intervention for SA2 and SA3. These models will also allow us to quantify the differences between the two study sites and differences between male and female by testing the interaction between study arm and site, and potentially the interaction between study arm and gender.

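### Community recruits enter on self-reported HIV infection, and an uninfected enrollee would count as a success on viral suppression: a modest dilution that is cheap to reduce

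*Protocol*

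**What the plan says.** In the Protocol, the eligibility list under *Screening and enrollment visit* sets the HIV criterion as "Confirmed to be HIV-infected by self-report". For people coming through community organisations or community referral, the same section says "GWU staff will ask individuals to confirm their HIV status". It then treats positive status as something to be confirmed before the screener is given, but it names no test, laboratory report, prescription or record.

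*Study procedures* lists the community routes, which include "local newspaper advertisements, electronic advertisements including Craigslist.com, fliers posted at frequently-visited venues, etc, as well as through street-based recruitment".

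Payment is stated in three places:
- *Baseline visit 2*: "Participants recruited in the community will receive a $50 incentive for completion of the baseline visit".
- The 12- and 24-week visits: "a $50 incentive for completion of the visit".
- *Monthly contact by phone/in-person*: $10 for each successful contact.

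The *Analysis Plan* names the "primary outcomes (plasma viral load suppression at Visits 2 and 3" and calls for intent-to-treat analysis. The planned blood tests are viral load and a baseline CD4 count. Community participants are randomised at the visit where the baseline sample is drawn, and viral load samples are shipped every two weeks, so no study result is in hand at randomisation.

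Participants are asked at enrolment for "consent for release of medical records from the DC DOC facilities and any community medical providers". *Baseline visit 2* provides for abstraction of the preceding 12 months of HIV care, where records can be obtained. After each follow-up visit, staff contact the medical provider for appointments, viral load, CD4 and prescriptions. The protocol does not say how a participant found not to be infected is handled.

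**The concern.** With most outcomes, a participant who does not have the disease adds noise. Here that participant adds a success. A person without HIV has no viral RNA and falls below any suppression threshold, so the test that defines the primary outcome cannot expose the mistake. The result looks the same as that of a well-treated participant.

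Detainees are referred by jail medical and discharge staff, described as referring HIV-positive inmates, in a system whose detention facility tests routinely. Community organisations are likewise described as referring HIV-positive clients. Neither filter covers someone who answers an advertisement, a flier or a street approach. Each uninfected enrollee raises the suppression rate in whichever arm they join, which narrows the contrast the trial is meant to measure.

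**Working it through.** **Inputs from the protocol.** Up to 150 participants allocated 1:1, so 150 / 2 = 75 per arm. The outcome is binary. The protocol gives no power, suppression rates, effect size or false-report rate, so there is no stated figure to reproduce.

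**Assumptions.** True suppression 50% (control) and 70% (intervention); two-sided 5% test; no dropout; uninfected share q of 2%, 5% or 10%, the same in both arms on average because assignment is random.

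**Dilution.** Every uninfected participant is scored as suppressed, so p′ = p(1 − q) + q. The difference becomes (1 − q) × (0.70 − 0.50).

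**Power.** Normal approximation with unpooled variance: SE = √{[p′c(1 − p′c) + p′t(1 − p′t)] / 75}, and power = Φ(difference / SE − 1.96).

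Example at q = 5%: p′c = 0.50 × 0.95 + 0.05 = 0.525; p′t = 0.70 × 0.95 + 0.05 = 0.715; difference 0.190; SE = √[(0.2494 + 0.2038) / 75] = 0.0777; 0.190 / 0.0777 − 1.96 = 0.484; power 0.686.

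| q | Control | Intervention | Difference (points) | Power |
|---|---|---|---|---|
| 0 | 50.0% | 70.0% | 20.0 | 72% |
| 2% | 51.0% | 70.6% | 19.6 | 71% |
| 5% | 52.5% | 71.5% | 19.0 | 69% |
| 10% | 55.0% | 73.0% | 18.0 | 65% |

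**Other assumed rates.** With 40% against 60% and a pooled-variance test, power is 69% at q = 0 and 67%, 65% and 60% at the same three values of q. The pattern does not depend on the pair chosen.

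**What q means for community recruits.** If nearly all false reports come from them, overall q = (community share) × (false-report rate among them). The protocol does not give the community share. If it were one half, an overall 10% would need 0.10 / 0.50 = 20% of community recruits to be uninfected, and an overall 5% would need 10%.

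**Chance imbalance.** The variance p′(1 − p′) already covers random variation in how many uninfected people fall in each arm. At q = 5% it is slightly smaller than at q = 0: 0.250 to 0.249 in control and 0.210 to 0.204 in intervention. No further term is needed.

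**Timing of the checks.** Record abstraction and provider contact both follow enrolment and depend on a signed release and on obtainable records. Neither is linked to eligibility or to a rule for the analysis. The baseline PVL is informative in one direction only: a detectable result shows infection, while an undetectable one leaves the question open.

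**The case against.** The strongest reply is that the protocol does not rely on viral load alone. Someone with undetectable virus at baseline, no HIV prescription and no HIV care record would stand out once charts and providers had been consulted. Staff also confirm release from a correctional facility within six months, open advertising is one route among several, and the screener itself is in an appendix that is not shown. At 2% to 5% uninfected, the loss is 0.4 to 1.0 points of effect and roughly 1.5 to 4 points of power. A strict paperwork requirement could disrupt the single-visit community baseline and shut out people not in care, in a trial about linkage to care. The transition models in the *Analysis Plan* condition on the prior outcome, which partly separates people already suppressed at baseline. A rule for uninfected participants may also sit in a statistical analysis plan that is not shown.

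Most of this stands, and it limits the size of the point and shapes the remedy. It does not remove the point. The checks are partial and come too late to affect entry, and the transition models are only one of three model structures that may be used.

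Three stronger readings are tempting, and the documents do not support them:
- *The error biases the trial toward one arm.* Assignment is random and follows enrolment, so the expected effect is dilution toward no difference.
- *Chance imbalance in false enrollees is a further harm.* It is already inside the power figures.
- *False enrolment would go wholly undetected, or is common.* Post-enrolment checks exist, and the protocol gives no rate.

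**Conclusion.** The point holds as a modest weakness in the eligibility rule. As written, openly recruited and paid community participants can be randomised on their word alone, and any who are uninfected become automatic successes on the primary outcome in either arm. Under the assumed 50% against 70% with 75 per arm and no dropout, the cost is 0.4 to 2.0 points of effect and about 1.5 to 8 points of power as the uninfected share runs from 2% to 10%. Both that share and the suppression rates are assumptions, and the upper end requires a high false-report rate among community recruits. The scoring itself is an inference, because the protocol states no suppression threshold, but an uninfected person would fall below any threshold. The point is worth acting on because the remedy uses material the trial already plans to collect.

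**What to change.** 1. For community recruits, replace self-report in the eligibility line with any readily available proof at screening: a laboratory report, an HIV prescription or medication bottle, a clinic or correctional record, or confirmation by a provider or community organisation.
2. Where none is at hand, still allow enrolment, so that people out of care are not excluded and the one-visit baseline is kept. Staff blind to arm then classify infection as documented or not, using only pre-randomisation records and the baseline PVL, where a detectable result counts as proof.
3. Keep the intent-to-treat primary analysis, and pre-state a sensitivity analysis of PVL suppression that excludes participants without documented infection. Limiting the evidence to the period up to the baseline draw, and blinding the classification, keeps the exclusion from depending on what happens after assignment. It should remain a sensitivity analysis because it will also drop some infected people who have no papers.

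Cost: one amended eligibility line with ethics review, slight delay at screening, and a little extra record and analysis work. No new laboratory test is needed.
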